### Self-administered retrospective questionnaire

At termination of the objective diurnal measurements, a self-administered questionnaire is applied regarding specific recall of time sitting during the measurement period. Time spent sitting during working hours is obtained by the question: ‘during working hours in the measuring period, in average per day, how long time did you spent sitting?’ [5-7,11] reported in hours and minutes. The longest continuous time with uninterrupted sitting is obtained from the question: ‘during working hours in the measuring period, how long is the longest uninterrupted time you have spent sitting?’ reported in hours and minutes. Both questions are also asked for leisure time before/after a workday and leisure time on a complete leisure day [7,11]. The questions used in this study are inspired both by International Physical Activity Questionnaire (IPAQ) [11] and Medical Outcomes Study Patient Assessment Questionnaire MOSPAQ [5,24] (modified Occupational Physical Activity Questionnaire (OPAQ) to specially measure sitting time) together with the new possibilities of the improved objective measurements, that allow specific measurement of sitting during work and leisure time.

#### Anthropometric measures

Height is measured without shoes to the nearest centimeter; weight is measured in light clothing without shoes to the nearest 0.1 kg (OBH Nordica, Slim Light, 150 kg; Taastrup, Denmark); waist circumference is measured midway between the lower rib margin and the iliac crest to the nearest 0.5 centimeter, without any pressure to the skin and with an unstretched tape measure; hip circumference is measured at the point yielding the maximum circumference over the buttocks to the nearest 0.5 centimeter. The tape should be held in a horizontal plane touching the skin but not indenting the soft tissue. Body mass index (BMI, kg/m^2^) and waist-hip ratio are calculated.

#### Serum lipids

A venous blood sample will be drawn (not fasting). Total cholesterol, high-density lipoprotein cholesterol (HDL), and triglycerides will be measured by an enzymatic method on the Vitros 5.1 FS from Ortho Clinical Diagnostics (Birkerød, Denmark). Low-density lipoprotein cholesterol (LDL) and very low-density lipoprotein cholesterol (VLDL) will be calculated by the formulae:$$ VLDL = Triglyceride \times 0.45 $$$$ LDL = Total\  cholesterol - HDL + VLDL $$

In addition, C-reactive protein (CRP) and glycosylated hemoglobin, type A1c (HbA1c) will be measured on Vitros 5.1 FS (Birkerød, Denmark) and G8 HPLC Analyzer from TOSOH (Aarhus, Denmark).

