### Objectives

The primary objective of this trial is to investigate the efficacy of an individually tailored, theory-based motivational counseling intervention on reducing daily sitting time in sedentary patients with RA. The secondary objectives are to explore whether a reduction in daily sitting time is related to reduction in pain and fatigue, improved health-related quality of life (HR-QoL), self-reported physical function, self-efficacy and improved cardiovascular biomarker levels, and to assess the cost-effectiveness of the intervention.

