## Discussion

This trial protocol describes the design of an innovative randomized controlled trial, which aims to test whether sedentary behavior can be reduced in patients with RA through behavioral lifestyle change. To the best of our knowledge, this is the first randomized trial to investigate the effect of an individually tailored motivational counseling intervention on daily sitting time in patients with RA. The intervention is developed and based upon results from studies in population-based samples of sedentary adults and in elderly and obese sedentary populations. The population under study, men and women with RA, represents a group of patients with chronic disease and increased risk of developing diabetes and cardiovascular diseases. In addition, a large proportion of patients with RA struggle with strained joints and immobility in daily life. If effective, the intervention may reduce the risk of cardiovascular disease and type 2 diabetes in patients with RA by reducing their daily sitting time. It should be noted that a possible reduction in sitting time, the primary outcome, does not necessarily imply a reduction in cardiovascular disease (CVD) risk. However, a possible effect of the intervention on secondary outcomes, CVD biomarkers (cholesterol and so on) will be simultaneously registered and studied.

We cannot rule out that wearing an ActivPAL® may cause reactivity and as such in itself act as a ‘behavioral intervention’. However, participants in both groups are measured at baseline and follow-up, and the size of the between arm difference is, therefore, not likely to be affected or considered in the sample size calculation. Also ActivPAL® monitors start measuring from midnight following the first day of application in order to minimize reactivity by allowing participants to get used to wearing the device. Finally, the ActivPAL® measurements are not shown to participants until after the study is completed.

It should be noted that in behavioral intervention RCTs patients are difficult to blind. We could have offered the control group participants a ‘sham’ counseling intervention with counseling on something else than reduction of sedentary behavior. However, this could potentially induce an effect in the control group which we wanted to avoid.

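### The printed LDL formula adds VLDL where it should subtract it; applied literally, it overstates each calculated LDL value by 0.9 × triglycerides

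*Protocol article*

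**What the plan says.** The Serum lipids section of the protocol article separates what is assayed from what is derived. On the assayed side: "Total cholesterol, high-density lipoprotein cholesterol (HDL), and triglycerides will be measured by an enzymatic method". On the derived side: "Low-density lipoprotein cholesterol (LDL) and very low-density lipoprotein cholesterol (VLDL) will be calculated by the formulae". Two formulae follow. The first sets VLDL to triglycerides multiplied by 0.45. The second sets LDL to total "cholesterol - HDL + VLDL", with an explicit plus sign before VLDL and no brackets.

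No other part of the article gives a different LDL formula or mentions a direct LDL assay, so this line is its only definition of LDL. Table 1 schedules LDL and VLDL at baseline, at the end of the intervention, and at 6 and 18 months post-intervention.

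The Objectives section refers in general terms to "improved cardiovascular biomarker levels". The Discussion places such markers among the secondary outcomes: "a possible effect of the intervention on secondary outcomes, CVD biomarkers (cholesterol and so on) will be simultaneously registered and studied".

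**The concern.** HDL, LDL and VLDL are parts of total cholesterol. Once HDL and VLDL are known, LDL is what is left after both are taken away. The printed rule takes HDL away and then adds VLDL back on top, so it returns an LDL larger than the whole of non-HDL cholesterol, of which LDL is only a part.

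At stake is the correctness of one derived lipid variable and of its between-group comparison. The error is not a fixed offset. It is proportional to each patient's triglycerides at each visit, so it drops out of the comparison of arms only to the extent that triglycerides are the same in both.

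**Working it through.** **Inputs.** From Serum lipids: VLDL = 0.45 × TG, and LDL as printed = TC − HDL + VLDL (TC total cholesterol, TG triglycerides). The section states no units; mmol/L and all lipid values below are assumptions for illustration. The sign error and its size of 2 × VLDL hold in any unit.

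**Step 1: the identity.** TC = HDL + LDL + VLDL, so LDL = TC − HDL − VLDL = TC − (HDL + VLDL). The printed line, read in the usual order of operations, does not follow from this.

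**Step 2: size of the error in one value.**
Printed − correct = (TC − HDL + VLDL) − (TC − HDL − VLDL) = 2 × VLDL = 2 × 0.45 × TG = 0.9 × TG.

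With assumed TC 5.0 and HDL 1.5:

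| TG | VLDL | LDL as printed | LDL correct | Excess | Excess, % of correct |
|---|---|---|---|---|---|
| 0.8 | 0.360 | 3.860 | 3.140 | 0.72 | 23 |
| 1.5 | 0.675 | 4.175 | 2.825 | 1.35 | 48 |
| 2.5 | 1.125 | 4.625 | 2.375 | 2.25 | 95 |
| 4.0 | 1.800 | 5.300 | 1.700 | 3.60 | 212 |

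**Step 3: do the fractions add back?** At TG 1.5, HDL + VLDL + printed LDL = 1.5 + 0.675 + 4.175 = 6.35, against a total of 5.00. With the correct LDL the sum is 1.5 + 0.675 + 2.825 = 5.00.

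**Step 4: effect on the between-group comparison.** Printed LDL = correct LDL + 0.9 × TG for every patient. The difference in group means is therefore the correct difference plus 0.9 × the between-group difference in mean TG:

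| TG difference between groups | Bias in LDL difference |
|---|---|
| 0.1 | 0.09 |
| 0.2 | 0.18 |
| 0.3 | 0.27 |
| 0.5 | 0.45 |

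The Statistical analysis section plans an ANCOVA with the baseline value as covariate. Randomization makes the expected baseline difference zero, so the expected bias is still 0.9 × the follow-up TG difference. Baseline adjustment does not remove an error that tracks triglycerides at the follow-up visit.

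**Step 5: direction.** With TC and HDL held fixed, LDL changes by +0.45 per unit of TG as printed and by −0.45 when correct. If instead VLDL falls by d while the other fractions stay as they are, TC also falls by d: correct LDL does not change, and printed LDL falls by 2d.

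**The case against.** The strongest reply is that this may be a typesetting slip. One pair of brackets, TC − (HDL + VLDL), makes the printed string exactly right, and a lost bracket is at least as plausible as a mistaken derivation. The laboratory may calculate LDL correctly whatever the article prints. This stands: harm to the trial's data is conditional on someone applying the line literally, and the article cannot show whether anyone would. It does not rescue the line itself, which is the only stated definition of a scheduled outcome. Nor can the point be left to an unseen analysis plan, because the formula is stated wrongly, not omitted.

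A second reply is that the percentages for single values overstate the effect on the trial's result. This also stands. The article reports differences between group means, and the shared part of the error cancels; only the triglyceride difference between arms carries through. Nothing in the article suggests that this difference will be large.

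Four stronger readings are tempting, and the article does not support them:

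- **That every LDL value the trial reports will be wrong.** This follows only from literal use of the line.
- **That a fall in triglycerides would show as a fall in LDL when the true LDL rises.** This needs total cholesterol and HDL held fixed, which is not the general case (step 5).
- **That non-fasting sampling makes the plus sign add noise.** With total cholesterol and HDL fixed, triglycerides enter with a coefficient of absolute size 0.45 under either sign. Beyond that, the answer depends on how the components vary together, which the article does not give. Non-fasting sampling is an openly stated design choice.
- **That LDL is itself named in the secondary objective.** The Objectives section speaks only of cardiovascular biomarkers; LDL is named in Serum lipids and Table 1.

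**Conclusion.** The LDL formula is wrong as printed and should subtract VLDL. If it is applied literally, each LDL value is too high by 0.9 × triglycerides, and the between-group LDL difference is biased by 0.9 times the between-group triglyceride difference. The algebra rests only on total cholesterol being the sum of its three fractions and on the article's own factor of 0.45; the numerical examples also rest on assumed lipid values and units.

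The reach is narrow. One derived secondary cardiovascular biomarker is affected, at four visits. The primary outcome (ActivPAL sitting time), the sample size, the measured total cholesterol, HDL and triglycerides, and the calculated VLDL are untouched. This is a definite error to correct, not a threat to the trial's main conclusion.

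**What to change.** Replace the line with LDL = Total cholesterol − HDL − VLDL, or equivalently Total cholesterol − (HDL + VLDL). Confirm that both the laboratory's calculation and the analysis code use this form. Recompute any LDL already derived with the plus sign from the stored total cholesterol, HDL and triglycerides.

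The cost is one line of text, at most one line of code, and a query to the laboratory. No new data are needed, and the correction requires no change to sampling and no additional lipid outcome.

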#### Blood pressure

Blood pressure will be measured, after 5 to 10 minutes of rest, 3 times at the right upper arm (average of the 3 measurements) with the participant in a sitting/lying position.

#### Additional information

In addition, information regarding demographics, lifestyle, time of diagnosis, consumption of pain killers and comorbidity (which are diabetes, hypertension, heart attack, stroke, chronic obstructive pulmonary disease (COPD), cancer, osteoarthritis, osteoporosis, asthma and depression) will be obtained; all self-reported. Information about DAS 28 (Disease Activity Score Based on 28 Joints and 4 variables including CRP [54], actual medical treatment and status of RA (for example, IgM-RF (rheumatoid factor of the immunoglobulin M class and/or ACPA (anti-citrullinated protein antibody)) will be obtained from the DANBIO registry [37] and the medical record.

#### Cost data

For the analysis of intervention costs, activities related to the intervention will be registered for each individual patient by the health care providers. In addition, data will be collected on time use related to each activity and relevant unit cost of resources. Other resource use and costs related to health care provisions will be obtained for each patient from the national health registries for hospitals, primary care, and purchase of prescription medication will be obtained from primary care pharmacies. These data will be obtained from the National Board of Health. Due to the confidentiality of these data (prescription data) they will be stored and analyzed through Statistics Denmark’s Research computer.

### Participant timeline

The trial will last 22 months including a 16-week intervention, and 6 and 18 months follow-up (Figure 1).

### Data collection

Measurements will be repeated 4 times during the 22 months: 1) at baseline; 2) at the end of the intervention (16 weeks after intervention start); 3) 6 months post intervention and finally (4) 18 months post intervention (Table 1). At each time point patients will complete self-reported questionnaires regarding demographics, lifestyle, sitting time at work and in leisure time, physical activity, physical function, pain, fatigue, health-related quality of life (HR-QoL) and general self-efficacy. Blood pressure, height, weight, waist circumference will be measured subsequently. Blood samples will be drawn and stored at the Department of Diagnostics, Division of Clinical Biochemistry, Glostrup Hospital, University of Copenhagen.

**Table 1 Tab1:** **Collection of patient characteristics and outcome measures**

	**Screening**	**Baseline**	**4 months by end of intervention**	**6 months post intervention**	**18 months post intervention**
Background					
Marital status		X			
Age		X			
Country of birth		X			
Cohabiting		X			
Level of education		X			
Employment status		X			
Annual household income		X			
Health-related issues					
Smoking		X	X	X	X
Alcohol consumption		X	X	X	X
Medical history					
Diagnosed with RA	X				
Actual treatment for RA		X	X	X	X
DAS 28		X	X	X	X
IgM-Rheumatoid Factor		X			
ACPA		X			
Co-morbidities					
Diabetes		X	X	X	X
Hypertension		X	X	X	X
Heart attack		X	X	X	X
Stroke		X	X	X	X
COPD		X	X	X	X
Cancer		X	X	X	X
Osteoarthritis		X	X	X	X
Osteoporosis		X	X	X	X
Asthma		X	X	X	X
Depression		X	X	X	X
Medicine					
Consumption of painkillers		X	X	X	X
Serum lipids					
Total cholesterol		X	X	X	X
High-density lipoprotein cholesterol (HDL)		X	X	X	X
Triglycerides		X	X	X	X
Low-density lipoprotein cholesterol (LDL)		X	X	X	X
Very low-density lipoprotein cholesterol (VLDL)		X	X	X	X
C-reactive protein (CRP)		X	X	X	X
HbA1c		X	X	X	X
Anthropometric measures					
Weight		X	X	X	X
Height		X			
Blood pressure		X	X	X	X
Waist circumference		X	X	X	X
Body mass index; BMI		X	X	X	X
Daily sitting time					
Measured total sitting time in hours and minutes (measured by ActivePAL®)		X	X	X	X
Self-reported daily sitting time (measured by physical activity - PAS, item 4)	X	X	X	X	X
Questionnaires (self-reported)					
Physical Activity Scale - PAS	X	X	X	X	X
Fatigue - MFI		X	X	X	X
Pain - VAS		X	X	X	X
Physical function - HAQ	X	X	X	X	X
HR-QoL - SF-36		X	X	X	X
HR-QoL - EuroQol/EQ-5D		X	X	X	X
General Self-Efficacy Scale - GSES		X	X	X	X
Specific questions on sedentary behavior at work and leisure		X	X	X	X

Table 1 shows the procedure of collecting data (objectively measured and self-reported) about the trial patients from baseline to 18 months follow-up.

Anti-CCP, anti-citrullinated peptide antibody; DAS 28: Disease Activity Score Based on 28 Joints; GSES: The General Self-Efficacy Scale; HAQ: Health Assessment Questionnaire; HR-QoL, health-related quality of life; MFI: Multi-dimensional Fatigue Inventory; RA: rheumatoid arthritis; SF-36: The Short Form [36] Health Survey.

Baseline demographic characteristics of patients are collected (electronically) via a self-report questionnaire (using tablets). Two occupational therapists will attach the ActivPAL® monitor [41] and instruct patients in how to wear the monitor 24 hours per day for 7 days. All ActivPAL® will be coded to start from midnight following the first day of application. One week (7 days) after baseline measurements the patient will return to the hospital for removal of the ActivPAL®. At the same time the patient will be informed by the Project Leader (TT) about the group allocation. One week after each of the follow-up measurements the patients will return the ActivPAL® in a closed envelope. During each 7 day-period with ActivPal® the patients fill a diary about their resting time and sleeping time in order to isolate their sitting time from sleeping time. At each medical visit to the outpatient clinic, the treating rheumatologist registers information in DANBIO including data regarding disease characteristics (for example, patient-reported outcomes, disease activity, functional status, disease course) and medical treatment [37]. Patients will not be blinded to the intervention; however, all assessors will be blinded for the two participating groups.

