## Methods

### Trial design

The current study is part of the ‘Joint Resources’ research program devoted to health promotion studies in patients with RA [30,31] and initiated in 2009 at Glostrup Hospital. The study is designed as a randomized, controlled, observer-blinded trial with two parallel groups and a primary endpoint of changes in objectively measured daily sitting time. Patient-reported outcomes and other measured variables will be collected before randomization, soon after the intervention (after 16 weeks), and 6 and 18 months post-intervention. Randomization will be performed with a 1:1 allocation (blocks of 10 patients) [32].

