### Randomization and blinding

Immediately following the baseline measurements, randomization to either (A) the intervention group (N = 75) or (B) the control group (N = 75) will be performed via computer-generated ‘random numbers’ for each of the 2 groups (blocks of 10 patients). Patients will be informed by TT about their group allocation 1 week after baseline measurements. Patients will not be blinded to the intervention; however, all measurements will be conducted by two occupational therapists who will be blinded to group allocation.

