### Primary outcome measure

Change in total daily sitting time in minutes [41,42] from baseline to 16 weeks.

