#### Changes in objectively measured sitting time

Measurements will be obtained using an ActivPAL® 3 TM Activity Monitor (PAL Technologies, Glasgow, UK). This is a small (2.0 × 1.4 × 0.3 inches) and light (20.1 grams) uniaxial accelerometer-based device [43] that is worn anteriorly on the upper right thigh and kept in place by waterproof dressing and adhesive tape. The monitor registers total physical activity level over a 7-day period. The monitor uses accelerometer-derived information about thigh position to estimate time spent in different body positions (that are sitting/lying, standing and walking; sleeping time will be deducted from data). Data will be processed as 0.1 second events data using the ActivPAL® software (version 6.4.1; PAL Technologies, Glasgow, UK). The ActivPAL® monitor has previously been validated against direct observation and compared with the Actigraph® GT3X Activity Monitor accelerometer (Pensacola, FL, USA) [42,44]. It is currently considered the best choice for objective measurement of sitting/lying. The ActivPAL® has also been found sensitive to change in sitting time [44].

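### The objectively measured primary outcome depends on sleep times from a diary kept by patients who know their allocation at 16 weeks, and no diary-free analysis is planned

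*Protocol article*

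**What the plan says.** The Trial design section names "a primary endpoint of changes in objectively measured daily sitting time". The Primary outcome measure section defines it as "Change in total daily sitting time in minutes" from baseline to 16 weeks.

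The section on objectively measured sitting time says that the monitor distinguishes sitting/lying, standing and walking, and that "sleeping time will be deducted from data". The Data collection section gives the source of the sleep times: in each 7-day wear period "the patients fill a diary about their resting time and sleeping time in order to isolate their sitting time from sleeping time". No other source is named.

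On blinding, the Data collection section states: "Patients will not be blinded to the intervention; however, all assessors will be blinded for the two participating groups". It also says that patients learn their group when they return for removal of the monitor one week after baseline; the Randomization and blinding section gives the same timing.

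The Statistical analysis section plans an ANCOVA with a factor for group and the baseline value as covariate. The Discussion considers reactivity to wearing the monitor and the difficulty of blinding patients. It does not mention the diary.

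**The concern.** In a trial with unblinded patients, a device-measured endpoint is the main protection against biased reporting. Here the protection is partial. The device supplies sitting/lying time, and a self-report decides how much of it is taken away as sleep.

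The arms are not in the same position when they fill in the 16-week diary. Intervention patients have had three counseling sessions and set personal goals for sitting less. Controls have been encouraged to keep their usual lifestyle. If one arm places bedtime a little earlier, rising a little later, or logs a daytime rest as sleep, its sitting time falls with no change in posture. In the reported result this would look the same as a real reduction. The blinded assessors do not complete the diary, so their blinding does not help.

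**Working it through.** **The plan's own figures.** Inputs from the Feasibility study and power calculation section: SD 1.7 h × 60 = 102 min, target difference 50 min, two-sided 0.05, pooled two-sample t-test. With the noncentral t distribution, 66 per group gives 79.8% power and 67 gives 80.4%, so 67 is the smallest size reaching 80%. With 75 per group the power is 84.7%. Both stated figures reproduce, and the sample-size arithmetic contains no error.

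**How diary error enters.** Let M be monitor sitting/lying time per day, S true sleep within it, and e the diary error in that sleep. The outcome is

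Y = M − (S + e) = (M − S) − e.

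If the mean of e at 16 weeks is b minutes higher in the intervention arm, the estimated difference (intervention minus control) is the true difference minus b. Error common to both arms cancels. Only diary sleep that overlaps recorded sitting/lying counts: if the diary only sets a window, standing or walking minutes inside it were never sitting time and are not deducted from it.

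**Why baseline does not remove it.** The baseline-adjusted difference is

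(difference at 16 weeks) − β × (difference at baseline),

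with β = 1 for a change score and β estimated in the ANCOVA. The baseline diary is filled in before disclosure, so under randomization its error has the same expectation in both arms and the baseline difference has expectation zero. Whatever β is, b stays.

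**Size over an assumed range.** The document gives no value for b. With SD 102 and 75 per group:

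- Standard error = 102 × √(2/75) = 16.7 min.
- Smallest significant difference = 1.976 × 16.66 = 32.9 min.
- Rejection probabilities come from the noncentral t with 148 degrees of freedom and noncentrality (difference)/16.66.

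| Assumed b (min/day) | Share of 50 min | Rejection rate, no true effect | Power, true effect 50 min, error against the intervention |
|---|---|---|---|
| 0 | 0% | 5.0% | 84.7% |
| 5 | 10% | 6.0% | 76.6% |
| 10 | 20% | 9.2% | 66.5% |
| 15 | 30% | 14.6% | 55.1% |
| 20 | 40% | 22.2% | 43.2% |
| 30 | 60% | 43.2% | 22.2% |

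These use the SD of the sample-size calculation. If the ANCOVA brings the residual SD below 102, the same b gives a higher false-positive rate.

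**The case against.** The strongest reply is that the risk is conditional. Patients are asked about sleep and rest, not about sitting. Nothing says they are told that reported sleep is subtracted, and monitor results are withheld until the study is over. The text does not say that diary times are used unchecked, event-level data exist, and an article may leave the processing algorithm to a fuller plan. A purely monitor-based rule has faults too: restless nights break up the longest lying bout, and the intervention itself targets long sitting bouts, so misclassification could also differ by arm.

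Most of this stands. It rules out calling the outcome biased, and it argues against simply replacing the diary in the primary analysis. It does not answer the narrower point: the article itself names the diary as the means of separating sitting from sleep, and differential error needs no deliberate distortion. The Discussion's argument that both groups are measured covers only influences that are equal in the two arms.

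A reader might infer three further faults that the document does not support.

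- **Rest is deducted.** The diary records rest, but the text deducts only sleep, which agrees with the Background's definition of sedentary behavior as waking sitting or reclining. No contradiction follows.
- **A part day distorts the mean.** At baseline the monitor is "coded to start from midnight following the first day of application" and removed after seven days, which leaves six full days and a part day. No text says that the part day is averaged as a full one, and such an error would affect both arms alike.
- **Total minutes should be standardized to waking time.** Total minutes is a legitimate endpoint and matches the sample-size basis. A percentage of waking time would be a different estimand.

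**Conclusion.** The point holds as a risk of bias in the primary comparison. It rests on three things the document states: sleep is deducted from sitting/lying time, the only named source of sleep is a patient diary, and the 16-week diary follows disclosure while the baseline diary precedes it. Any between-arm difference in diary error, within recorded sitting/lying time, passes into the estimate at full size, and neither baseline adjustment nor assessor blinding removes it.

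A reader might go further and conclude that the effect will be biased, or biased by a known amount. The document supports neither: it shows no difference in diary reporting and gives no figure for one. The range of 5 to 30 min/day, and the rejection rates of about 6% to 43% that follow, are assumptions that show sensitivity. They are not estimates.

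**What to change.** Keep the planned primary analysis and add the following to the plan:

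- **A diary-independent analysis** of the 24-hour recording, processed blind to group and reported beside the primary result. Candidates are 24-hour sitting/lying time, upright time (standing plus walking), or sitting time with a monitor-derived sleep window. Choose one in advance.
- **Diary sleep and waking time by arm**, at baseline and at 16 weeks.
- **A reading rule set in advance.** A fall in sitting time matched by a similar rise in upright time supports a real change. A fall that comes with more diary sleep and no rise in upright time does not, without further evidence. Neither 24-hour sitting/lying nor upright time can separate longer true sleep from longer reported sleep; a monitor-derived sleep window helps there.

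The monitor is already worn around the clock, so no new data are needed. The cost is a little more processing, and a monitor-derived sleep window may misclassify restless nights or long daytime rests. That is why it belongs beside the primary analysis and need not replace it.
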